## Abstract

**Background:**

Clinic non-attendance rates are high across the African continent. Emerging evidence suggests that phone-based reminder messages could make a small but important contribution to reducing non-attendance. We will use behavioural economics principles to develop an SMS and voice reminder message to improve attendance rates in a school-based eye screening programme in Botswana.

**Methods:**

We will test a new theory-informed SMS and voice reminder message in a national school-based eye screening programme in Botswana. The control will be the standard SMS message used to remind parents/guardians to bring their child for ophthalmic assessment. All messages will be sent twice. The primary outcome is attendance for ophthalmic assessment. We will use an automated adaptive approach, starting with a 1:1 allocation ratio.

**Discussion:**

As far as we are aware, only one other study has used behavioural economics to inform the development of reminder messages to be deployed in an African healthcare setting. Our study will use an adaptive trial design, embedded in a national screening programme. Our approach can be used to trial other forms of reminder message in the future.

**Trial registration:**

ISRCTN 96528723. Registered on 5 January 2022.

**Supplementary Information:**

The online version contains supplementary material available at 10.1186/s13063-022-06519-y.

## Administrative information

Note: the numbers in curly brackets in this protocol refer to SPIRIT checklist item numbers. The order of the items has been modified to group similar items (see http://www.equator-network.org/reporting-guidelines/spirit-2013-statement-defining-standard-protocol-items-for-clinical-trials/).

## Introduction

### Background and rationale {6a}

Many health programmes experience large mismatches between those identified with a clinical need and those who attend services. A recent international systematic review of ‘no-show’ appointments across all medical specialities in primary and secondary care estimated that 23% of clinic appointments are not attended, with the highest rate observed in the African continent (43%) [1]. Complex supply and demand factors govern access to health services [2], and systematically marginalised populations are often the least likely to receive care [3, 4].

As mobile phone penetration has risen, there has been increasing interest in the use of phone-based reminder messages to reduce these missed appointments. Systematic reviews from 2011 [5], 2013 [6], 2016 [7], 2018 [8], and 2019 [9] have found that SMS and voice message reminders can improve clinic attendance by 50–100% depending on service, population and setting. In Linde and colleague’s systematic review of African RCTs, their pooled analysis found that SMS reminders doubled appointment attendance compared with no SMS (odds ratio 2.03; 95% confidence interval 1.40 to 2.95; *I*^2^ = 85%) [9]. Robotham and colleagues’ 2016 review found that two or more notifications increased attendance by as much as 19% over and above sending one notification, and voice notifications may offer slight improvements over text notifications for increasing attendance [7].

SMS and voice messages function as behavioural ‘brief interventions’, and a number of studies have used behavioural economics principles to guide the wording of these messages in order to optimise their impact [10, 11]. Senderey and colleagues used a set of established cognitive biases to develop the content of eight different clinic reminder messages [12] and Huf and colleagues used a similar approach in developing four different messages to boost clinic attendance in the UK [13]. Whilst both studies showed improvements in clinic attendance rates, neither provided the rationale for why these specific biases were selected. In Linde and colleagues’ 2019 systematic review of 31 African RCTs using phone-based messages [9], only one study reported using behavioural theories to develop the content of their reminder message: Erwin and colleagues successfully boosted cervical cancer screening rates among women in Tanzania [14], basing their SMS reminder content on the Health Belief Model [15]. They also reported using a motivational tone—found to be more effective than an informational tone [16]—and pre-tested the SMS content validity and cultural sensitivity of the message with programme staff and laypeople.

One area that currently experiences very high rates of missed appointments—with substantial societal and economic costs—is community-based vision screening. Approximately 1.1 billion people (over 10% of the global population) currently live with a form of easily correctable visual impairment [17, 18]. Two very cheap and simple interventions—spectacles and cataract operations—could eliminate over 90% of all visual impairment worldwide [17]. Provision of these services has risen exponentially in recent decades; however, effective coverage rates are disappointingly low and exhibit marked socioeconomic gradients at the international and intra-national levels [17]. Women and marginalised groups bear a disproportionate burden of visual impairment, and often face structural social barriers that prevent them from accessing care—as noted in the recent UN Resolution on Vision [19].

Recognising the human, social, and economic drag exerted by cataracts and uncorrected refractive error, many low- and middle-income country (LMIC) governments are ramping up their vision screening programmes. Donor funding is rising in tandem, partly driven by the advent of phone-based screening platforms like Peek Acuity [20, 21] that have made it possible to rapidly screen entire regions with very modest resource requirements.

Screening programmes based on the Peek digital platform are currently operating in seven LMICs. The Botswanan Ministry of Health (MoH) has committed to use Peek software to screen all school children in government schools over 3 years beginning in Summer 2022 [22]. The Peek platform records basic sociodemographic data, visual acuity, referral status, and attendance status for each child. Every time a child is referred a series of three SMS messages are sent to the mobile phone number registered by their parent/guardian (see Table 1). The current SMS message was not developed with reference to behavioural economics principles. According to internal data from Peek screening programmes in other countries and pilot data in Botswana, attendance rates are currently around 50%, i.e. only half of those identified as needing ophthalmic assessment present to services.

We aim to develop two behavioural economics-informed reminder messages; an SMS and a pre-recorded voice message to be used in the new Botswana MoH schools-based vision screening programme, and tested using an embedded, pragmatic, adaptive RCT design.

### Objectives {7}

Our objectives are to test a behavioural economics-informed SMS reminder message and a pre-recorded voice message that will be sent to the parents/guardians of school children who have been identified as having a visual impairment and referred to clinic. We hypothesise that these messages will be associated with a higher attendance rate than the current standard SMS reminder that is sent to all referred patients’ parents/guardians.

### Trial design {8}

This is an automated, adaptive, parallel, four-arm, embedded, pragmatic RCT. We will start by testing the two SMS reminder messages head-to-head with an initial 1:1 allocation ratio, and then introduce the voice messages after a period of six weeks. We will use a Bayesian adaptive trial algorithm to perform adaptive allocation as the trial progresses.

## Methods: participants, interventions and outcomes

### Study setting {9}

The Botswana National Comprehensive School Eye Health Program (‘Pono Yame’).

### Eligibility criteria {10}

Reminder messages will be sent to the registered mobile phone numbers of parents/guardians of children who test positive at screening and are referred on to clinic in the Pono Yame MoH/Peek Vision school screening programme in 2022. Provision of a mobile number is a pre-condition of entry into the screening programme, although parents/guardians are able to supply the number of a friend or relative so in practice this stipulation does not exclude any children.

Reminders will be sent in English and Setswana; spoken by >96% of the local population. The screening programme routinely collects data on preferred language, and reminders will be sent in the preferred tongue. Those who list any language other than English of Setswana will receive the reminder in both Setswana and English. The reminder will also be sent in both languages to those where data on language is not available for any reason. We will perform a secondary analysis that excludes these participants, but they will be included in the primary analysis.

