### Strategies to improve adherence to interventions {11c}

There are no relevant strategies to improve adherence. This is a pragmatic intention-to-treat study, and we will not collect data on whether messages were actually read or listened to by the intended recipients. A potential limitation of this study is that we cannot ensure that the message is actually delivered to- and read by the correct person. To an extent, this is true of all forms of phone-based reminder messages, as it is of paper reminder letters or notes sent by post, or home with children.

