### Sample size {14}

Approximately 1000 children will be screened every day. Based on previous programmes, we expect approximately 160 of these children to be identified as requiring referral for further assessment and treatment. All of these children’s parents/guardians would receive the standard SMS reminders in a standard programme.

The adaptive allocation method that we are using does not use a pre-specified a sample size. Instead, the study will run until one of two criteria is met:There is a >95% probability that one arm is best.There is a >95% probability that the difference between the arms remaining in the study is <1%.

Depending on the effect of the interventions, one of the stopping criteria might be met after a few days; however, it could also take years before reaching a definitive conclusion. We will set a 3-month limit for this current study due to resource constraints.

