### Recruitment {15}

Community sensitisation is being led by the Ministry of Health and Ministry of Education. This includes TV and radio coverage explaining the Pono Yame screening programme. Our field coordinator will visit each region and work with schools to ensure that they are set up to enrol as many children as possible. Every referred child’s data will be included in the primary analysis. Subgroup analyses will only be permitted for children whose parents have consented for their sociodemographic data to be used for research purposes. This is a separate consenting process led by Peek.

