### Assignment of interventions: allocation

#### Sequence generation, concealment and implementation {16a, 16b, 16c}

Participants will initially be randomly allocated into two arms using computer-generated blocks of 12. As allocation and intervention delivery (sending SMS messages) is fully automated, there is no need for any of the human investigators to know participant allocation status. Once the first participants attend refractive services, the algorithm will begin adjusting the allocation ratio to favour the best-performing arms. There is no need for the investigators to see allocation status at this stage either. The data safety monitoring committee will be fully unmasked to allocation status and all outcome data and will have the power to stop the trial or suspend any arm.

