### Data collection and management

#### Plans for assessment and collection of outcomes {18a}

Referral status, attendance status and days elapsed since referral will be collected using the Peek Capture system on Android devices. Every time a participant is referred and every time they attend at clinic, they are checked in using an android device operating Peek Capture software. Additional data on sociodemographic characteristics will be collected when participants initially present to the screening programme.

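### Children are allocated singly, but messages go to phone numbers that several children may share, so one phone can receive both SMS versions

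*Protocol article*

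**What the plan says.** **Delivery is to a phone.** Background and rationale {6a} describes the programme's routine: "Every time a child is referred a series of three SMS messages are sent to the mobile phone number registered by their parent/guardian". Eligibility criteria {10} sends the trial reminders to registered numbers too. It adds that "parents/guardians are able to supply the number of a friend or relative", so that the need for a number excludes no child. No rule requires one number per child.

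**Allocation and analysis are by child.** Under Sequence generation, concealment and implementation, "Participants will initially be randomly allocated into two arms using computer-generated blocks of 12", with an "initial 1:1 allocation ratio" (Trial design {8}) that later adapts. The participant is the child: "Every time a participant is referred and every time they attend at clinic, they are checked in using an android device" (Plans for assessment and collection of outcomes {18a}). For the analysis, "Every referred child’s data will be included in the primary analysis" (Recruitment {15}). No sentence says outright that allocation is per child, but these sections read together leave no other natural meaning.

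**The stated limitation is a different one.** Strategies to improve adherence {11c} concedes that "we cannot ensure that the message is actually delivered to- and read by the correct person". That concerns a wrong or absent reader. It does not cover one phone receiving messages from two arms.

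**The concern.** The intervention reaches a phone, but the phone is not the unit of allocation. If two referred siblings, or two children registered under one relative's number, fall in different arms, the same adult holds both texts.

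Table 1 makes carry-over plausible. The new SMS says that the check-up costs nothing, that it covers every child at the school with an eye problem, and that schoolwork may suffer. It is signed by a doctor. The standard SMS has none of this. A parent who reads the new text about one child has read much of the active content for a sibling in the control arm.

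The expected direction is towards no difference. Dilution would delay the rule that one arm is best and favour the rule that the difference is below 1%. Because allocation moves towards the better arm, a control child's phone becomes more likely to carry the new message as the trial goes on.

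**Working it through.** The article gives no sharing rate, target effect or power, so there is no stated figure to reproduce. What follows is an illustration under stated assumptions.

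**Inputs**
- Referral rate: Sample size {14} says "we expect approximately 160 of these children to be identified as requiring referral for further assessment and treatment", out of about 1000 screened a day. 160/1000 = 16%.
- Share of children with one other screened child on the same number: 30% to 60% (assumed).
- Referral of the two children is independent (assumed).
- True difference between new and standard SMS: 5 percentage points (assumed).
- Carry-over is full, meaning that a control child whose phone also receives the new SMS responds as if allocated to it (assumed; an upper bound).

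**Step 1: share of referred children on a shared number, s**
- 0.30 × 0.16 = 0.048
- 0.60 × 0.16 = 0.096
- Ceiling of this one-sibling model, if every child shared with one other: 1.00 × 0.16 = 0.16

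**Step 2: dilution.** Let q be the probability that the other child on the number is in a new-SMS arm. Observed difference = true difference × (1 − s × q).

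| s | q = 0.5 (1:1) | q = 0.9 (assumed, after adaptation) |
|---|---|---|
| 0.048 | 5 × (1 − 0.024) = 4.88 | 5 × (1 − 0.0432) = 4.78 |
| 0.096 | 5 × (1 − 0.048) = 4.76 | 5 × (1 − 0.0864) = 4.57 |
| 0.16 (ceiling) | 5 × (1 − 0.08) = 4.60 | 5 × (1 − 0.144) = 4.28 |

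**Step 3: effect on the 1% rule.** At 1:1, a true difference is seen as less than 1 point if it is below 1/(1 − s × q). That is 1/0.976 = 1.02 points at s = 0.048 and 1/0.952 = 1.05 points at s = 0.096. Only a narrow band of true differences just above 1 point is pushed under the margin.

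**Step 4: what allocation by number does.** With all children on a number in one arm, s × q becomes 0 and the full difference is kept. Each pair then forms a cluster within an arm, and the variance is multiplied by about 1 + s × ICC. At the extreme ICC of 1 this is 1 + 0.048 = 1.05 and 1 + 0.096 = 1.10. For comparison, the information lost to dilution at 1:1 corresponds to a factor 1/(1 − s/2)²: 1/0.976² = 1.05 and 1/0.952² = 1.10.

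**The case against.** **The quoted sentence does not itself show two referred children on one number.** It explains why the need for a number excludes nobody. True, but siblings on a parent's own number are an ordinary case, and nothing shown prevents either kind of sharing.

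**A condensed article may leave repeat numbers to the full protocol or the code**, both of which it says can be obtained. This stands in part: if the software already groups children by number, the point falls. The article does, however, state the unit and method of allocation, and it contains no such grouping.

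**Each message names one child, with that child's place and date**, so carry-over may be far from full. This stands, and is why the figures are upper bounds for the stated sharing.

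**Allocation by number gains little precision.** This also stands. At ICC near 1 the clustering penalty about equals the information lost to dilution (step 4). The gain is the removal of a bias.

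Three stronger readings are tempting, and the documents do not support them:
- *A larger loss.* A reader might take 20% sharing and a three-in-four chance of different arms once four arms run, giving 5 × (1 − 0.20 × 0.75) = 4.25 points. But 20% exceeds the 16% ceiling above; it would need larger groups per number or correlated referral, and the article gives a basis for neither. The 0.75 does not fit the SMS contrast. Arms 1 and 3 carry the same standard SMS and arms 2 and 4 the same new SMS, so at equal allocation the chance is 0.5. Nor are four equal arms planned, since voice messages enter after six weeks of adaptation.
- *Linked outcomes counted as independent are a serious error as planned.* Under per-child allocation at 1:1, linked pairs fall in the same arm about as often as in different arms, so their covariance roughly cancels in the arm difference.
- *Allocation by number removes the linkage.* It places the linkage within an arm.

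**Conclusion.** The point holds as a cheap improvement to the design. Allocation is by referred child, delivery is to a number that may be shared, and nothing shown stops one phone from receiving both SMS versions. The expected consequence is a bias towards no difference, which grows on the control side as allocation shifts to the new message.

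The size is unknown and probably modest. Under the assumptions listed, at 1:1 an assumed 5-point effect loses about 0.1 to 0.2 points, and less if carry-over is partial. A conclusion would change only close to a stopping boundary. The direction is the expected one; the documents do not prove it.

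**What to change.** - **Allocation:** randomise the first referred child on each registered number and let later children on that number inherit the arm. Allocation is automated and the number is already held, so this is a lookup in the code. It is not randomisation by school.
- **Analysis:** let the final comparison allow for clustering by number, or repeat it with one child per number. The daily posterior would otherwise treat children on one number as independent; with variance inflation of at most about 1.05 to 1.10 this matters little, but it should be stated.
- **Reporting:** give the number of phone numbers that serve more than one referred child. If per-child allocation is kept, also report how many numbers received messages from more than one arm, and repeat the primary comparison without them.

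The costs are the clustering penalty, slightly uneven arm sizes, and a small lag in adaptation, because a later child inherits an arm drawn under an earlier ratio. According to the Trial status section, recruitment had not begun, so the change could be made before the first allocation.

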### Who will take informed consent? {26a}

The interventions represent minor modifications to existing routine processes and present negligible risk to participants. Obtaining consent would introduce burdens to the participant that are greater than the intervention itself. As such, we will not seek informed consent. This approach has been approved by the LSHTM and University of Botswana ethics committees, and follows the precedent set by three previous RCTs testing SMS reminder messages [12, 13, 23].

### Additional consent provisions for collection and use of participant data and biological specimens {26b}

All parents/guardians are verbally informed that their children will partake in the Pono Yame vision screening programme. They are also asked to provide written opt-out consent for the use of their children’s sociodemographic data for research and sharing purposes. Care will not be compromised in any way for those participants whose parents do not provide consent.

### Interventions

#### Explanation for the choice of comparators {6b}

The standard SMS message presented in Table 1 is routinely sent to the registered mobile phone of parents/guardians of children referred on for refractive services in all Peek programmes. This is the control arm.

**Table 1 Tab1:** Control and intervention reminder messages

**Control: Standard SMS reminder message** **Setswana** Go [name], one wa tlhatlhobiwa matlho mme ga fitlhelwa ona le bothata jwa matlho. Ka jalo, tla ko [location] ka di [date] go tlhatlhobiwa.O kopiwa go tla le karata ya gago ya botsogo. **English** Dear [name], you were examined and found to have an eye problem. Kindly report to [location] on [date] for assessment. Please come with your clinic card. **Intervention: New SMS reminder message** **Setswana** Go motsadi: Re lemogile ngwana wa gago [child’s name] fa ana le bothata jwa matlho. Se, se ka ama tiro ya gagwe ya sekolo. Tswee-tswee, tsisa [child’s name] ko sekolong ka [location and time] o tla tlhatlhobiwa matlho a sa duele Se, se direlwa ngwana mongwe le mongwe mo sekolong yoo nang le bothata jwa matlho Re ka leboga go le bona ka [day and time]. Kea leboga [Leina la ngaka] **English** Dear parent, we have found that your child [child’s name] has an eye problem. This may affect [his / her] schoolwork. Please bring [child’s name] to [location] at [time], [day, date]. We will be doing a free medical check-up for all the children with eye problems in the school. We look forward to seeing [child’s name] on [day and time]. Many thanks, Dr [name], Ministry of Health **Intervention: New voice reminder message** **Setswana** Dumelang: Ke bidiwa ngaka [name], go tswa ko lephateng la botsogo. Ngwana wa gago [leina la ngwna] o tlhatlhobilwe matlho mo bogaufing, mme a fitlhelwa a na le bothata jwa matlho. Fa a ka seka a alafiwa , go ka ama tiro ya gagwe ya sekolo. Setlhopha sa rona sa botsogo, se tlaa bo se le ko sekolong sa ga [leina la ngwana] ka [letsatsi le nako]. Tswee.tswee tsisa ngwana wa gago go tlhatlhobiwa go sena dituelo. Se, se direlwa ngwana mongwe le mongwe yoo nang le bothata jwa matlho. Kea leboga [Leina la ngaka] **English** Hello, my name is Dr [name] from the Ministry of Health. Your child [child’s name] recently had [his/her] eyes checked at school and was found to have an eye problem. If this is not corrected, it could affect their schoolwork. Our medical team will be at [location] on [date/time]. Please bring your child to get a free medical assessment. This is offered to all children with eye problems. We look forward to seeing you and your child on [date/time] Many thanks, Dr [name].	

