### Outcomes {12}

All children who are screened and found to need further assessment and treatment (e.g. refractive services) will be given an appointment, approximately 1 week later, at a specified field ‘triage and treatment’ clinic or at a specialist ophthalmic hospital clinic. The primary outcome is attendance at this pre-specified appointment on the appointment date (yes/no).

The Peek software retains a record of every referred child. When children attend for these appointments, they are checked in using Peek software. This automatically updates their attendance status. Attendance data will be automatically reviewed by an algorithm every 24 h. The great advantage of the Peek-based screening programme is that is a closed data system with complete, unified data records for every person screened, their referral status and their attendance status. No additional data collection activities are required.*Primary outcome*: attendance at clinic on invited date. This is a binary outcome measure (yes/no). We will compare mean outcome rates between arms.*Secondary outcome*: days elapsed between appointment date and attendance. This is because children may miss their appointed day but attend at a later date. We will compare mean number of days elapsed between each arm.*Subgroup analyses*: attendance by age, sex, urban/rural residence, distance to clinic, ethnicity, guardianship, religion, language, household composition, migrant status, parental occupation, housing, assets and income.

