#### Methods for additional analyses (e.g. subgroup analyses) {20b}

Internal data from a pilot site suggests that around 10% of children who attend the ‘triage and treatment’ clinic will subsequently be identified as having an eye need that requires further specialist ophthalmological assessment in a hospital clinic. These children will be referred from the ‘triage and treatment’ clinic to the local hospital. This subgroup will also receive either the intervention or control reminder messages. Again, the outcome will be attendance on appointed date.

Once the trial is complete, we will perform retrospective subgroup analyses to explore whether attendance within each group was associated with sociodemographic variables. We use multivariable logistic regression to assess whether each sociodemographic variable is associated with attendance. We note that this is an exploratory analysis, providing hypotheses that can be tested in subsequent studies.

We will perform a secondary analysis that excludes participants whose preferred language is neither Setswana nor English.

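### The final Setswana intervention messages do not match their English versions on venue and date, and conflict with hospital appointments, so they can lower on-date attendance for reasons unrelated to the behavioural wording

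*Protocol article*

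**What the plan says.** Table 1 (under Explanation for the choice of comparators {6b}) gives each message in both languages, and Intervention description {11a} calls these texts final.

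- **Control SMS, Setswana:** open location and date, "tla ko [location] ka di [date] go tlhatlhobiwa". The English control text has the same two fields.
- **New SMS:** the English directs the parent "to [location] at [time], [day, date". The Setswana has "ko sekolong ka [location and time] o tla tlhatlhobiwa matlho a sa duele" and closes with "Re ka leboga go le bona ka [day and time".
- **Voice message:** the English says "Our medical team will be at [location] on [date/time". The Setswana says "se tlaa bo se le ko sekolong sa ga [leina la ngwana] ka [letsatsi le nako".

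Outcomes {12} puts the appointment at a field triage and treatment clinic "clinic or at a specialist ophthalmic hospital clinic", and defines the primary outcome as attendance at that appointment on its date. About 10% of those who attend triage are referred on to hospital, and Methods for additional analyses {20b} states: "This subgroup will also receive either the intervention or control reminder messages". Under Eligibility criteria {10}, families get reminders in their preferred language. Both languages are sent only when the preference is something else or unknown.

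**The concern.** The trial compares wordings, so every arm should carry the same logistical content: where to go and when. Here the content differs by arm and by language. A Setswana-preferring family with a hospital appointment gets the correct place and date from the control SMS. The new SMS gives them a mixed instruction, and the voice call gives them the school. The primary outcome is exactly being at the right place on the right date, so the defect acts directly on the endpoint and sits only in intervention content.

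The design would not separate this from message performance. The algorithm reallocates daily on attendance alone, so misdirection would look like weak wording. The planned language analysis removes families who prefer neither language; it does not isolate Setswana readers. Section {11b} gives no formal option to modify the messages once running. The Setswana and English versions are also pooled as one intervention although they are not equivalent.

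**Working it through.** **Step 1. Fields side by side (Table 1).**

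| Text | Arms | Language | Venue | Day or date |
|---|---|---|---|---|
| Control SMS | 1, 3 | Setswana | location field | date field |
| Control SMS | 1, 3 | English | location field | date field |
| New SMS | 2, 4 | English | location field | day and date field, with time |
| New SMS | 2, 4 | Setswana | fixed *ko sekolong*, then a combined location-and-time field | day-and-time field only |
| Voice | 3, 4 | English | location field | date/time field |
| Voice | 3, 4 | Setswana | child's school; no location field | day-and-time field |

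That *sekolong* means school can be seen within Table 1: *mo sekolong* stands where the English SMS speaks of children in the school. That English phrase describes who is being checked; the venue in the English SMS is still the open field.

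**Step 2. Consequence by arm, for a Setswana-only family whose appointment is not at the child's school.**

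- Arm 1: correct place and date.
- Arm 2: the SMS says school, then inserts another location.
- Arm 3: the SMS is correct; the call says school.
- Arm 4: the SMS contradicts itself; the call says school.

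**Step 3. Scale.** The plan states no figure to reproduce, and Sample size {14} sets no sample size. An illustration:

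- Inputs from the documents: about 160 referrals a day ({14}); attendance about 50% (Background and rationale {6a}); about 10% of triage attenders sent to hospital ({20b}).
- Second-stage hospital appointments: 160 × 0.50 × 0.10 = 8 a day. Share of all appointments: v = 8 / (160 + 8) = 4.8%.
- Assumptions, not in the documents: s, the share receiving Setswana only; l, the share of would-be attenders lost when the venue is wrong or contradictory; 50% attendance at both stages; second-stage appointments counted in the same comparison.
- Loss in an intervention arm = s × v × l × 0.50.

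| v | s | l | Loss (points) |
|---|---|---|---|
| 4.8% | 50% | 25% | 0.3 |
| 4.8% | 80% | 50% | 0.96 |
| 4.8% | 100% | 100% | 2.4 |
| 25% (assumed) | 50% | 25% | 1.6 |
| 25% (assumed) | 100% | 100% | 12.5 |

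The 25% rows show what happens if some first referrals go straight to hospital or some field clinics are held away from the child's school. The documents give neither share. The yardstick is the second stopping rule, which treats a difference below 1% as no difference.

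**The case against.** Several points on the other side stand, and they limit what can be claimed.

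- **Venue in the SMS.** A reader might infer that both Setswana texts fix the venue as the school, or that families in arms 2 to 4 are simply told to go there. They are not. The new SMS also carries a location field, and arm 3's SMS is the standard one with the correct place and date. Only the voice text has no location field.
- **Date.** A reader might infer that the Setswana SMS leaves families without a day. It has a day-and-time field, the guidance cited in {11a} writes the day together with the date, and the SMS is repeated the day before the appointment. What remains is some ambiguity in the first copy, about a week ahead, if only a weekday is inserted. The voice text has a day-and-time field, so the date point does not reach it.
- **Sign-off.** The Setswana SMS omits the Ministry of Health, but Table 2 asks for a trusted official or professional and the doctor signs. The messenger element is present; this is a minor mismatch.
- **Field clinics.** The documents do not say where these are held. If they are at the child's school, the school wording is right for them, and the venue error is certain only for hospital appointments.
- **Quality control.** {11a} reports professional translation and back-translation, detailed in an appendix not shown. The deployed templates may differ from Table 1, and the reading here needs a Setswana speaker's confirmation.

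None of this removes the mismatch. The texts are called final, and the same messages go to families with hospital appointments.

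**Conclusion.** The point holds in limited form. The Setswana intervention texts are not equivalent to their English versions. For hospital appointments, and for any field clinic not at the child's school, the voice text names the wrong venue and the new SMS conflicts with itself. The exposed group is families who receive Setswana alone. Any effect on the primary outcome is to the disadvantage of the intervention arms, and the algorithm would count it as poor performance.

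The size cannot be fixed from the documents. Counting only second-stage hospital referrals, it is about 0.3 to 2.4 points, a range that spans the 1-point equivalence rule. The range depends on the assumed shares and on those appointments entering the main comparison. If they are analysed only separately, the effect on the primary result depends on the unstated share of first appointments held away from the school. A reader might want to quote one loss for the trial, or a wrong-day rate, but nothing in the documents supports either. The case for correction before launch rests on the texts themselves.

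**What to change.** Before recruitment:

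1. In both Setswana intervention texts, replace the fixed school wording with the location field used in the English.
2. Add an explicit day-and-date field to the Setswana SMS.
3. Add the Ministry of Health to the Setswana SMS sign-off, so that the two versions agree.
4. Have a Setswana speaker confirm the corrected texts by back-translation.
5. Generate each template in each language once for a field-clinic appointment and once for a hospital appointment, and check that place and date come out correctly and agree between SMS and voice.

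The cost is a template edit, re-recording of the Setswana voice message if it has already been recorded, a short translation check, and a minor notification to the ethics committees. No extra participants are needed. Trial status says recruitment has not begun, so no data would be affected.
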